### Health Economic Analyses

The cost-utility and cost-effectiveness of the intervention will be evaluated from a health service perspective. A Markov model will be developed using TreeAge Pro software (TreeAge Software Inc.), and the cycle length will be 1 month. Transition probabilities will be calculated using the intervention and control group data. The ratio of estimated total costs and differences in QALYs between baseline and postintervention for all participants will be used to estimate the incremental cost-effectiveness ratio (ICER) within the cost-utility analysis framework. The value for money of the provision of dental care to RACF residents will be assessed by comparing the estimated ICER with the willingness-to-pay threshold for a QALY. ICER will also be calculated based on the cost per incremental caries arrested to assess cost-effectiveness. A probabilistic sensitivity analysis will be conducted to determine the robustness of the cost-utility and cost-effectiveness findings to changes in factors affecting costs and outcomes.

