### Calculation of Cost and Utility Weights

The health economic analysis will be based on cost-effectiveness and cost-utility analysis frameworks. The costs associated with the intervention will be estimated using a bottom-up approach. Costs will be estimated as the product of unit costs and the quantity of resources (labor, materials, and services) used in the activities of this study. The treatment cost will include oral health examination cost, AgF application, and costs for any urgent conditions (eg, acute infections), and calculations will be based on the schedule of fees by the Australian Government Department of Veterans’ Affairs [41]. The main effectiveness measure will be quality-adjusted life years (QALYs), and the utility weights to generate QALYs will be informed by the EQ-5D-5L scores and the Australian utility weights for the EQ-5D-5L [42]. The improvement of oral health status (eg, number of caries arrested) will also be assessed as a secondary effectiveness measure.

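### As worded, the cost-utility ICER divides total costs by a baseline-to-follow-up QALY change, so neither term compares intervention with control

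*Protocol article*

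**What the plan says.** The Health Economic Analyses section of the protocol article describes the ratio as "The ratio of estimated total costs and differences in QALYs between baseline and postintervention for all participants will be used", and gives its purpose as "to estimate the incremental cost-effectiveness ratio (ICER) within the cost-utility analysis framework". Value for money is then judged by "comparing the estimated ICER with the willingness-to-pay threshold for a QALY".

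The same section plans a Markov model with 1-month cycles and says "Transition probabilities will be calculated using the intervention and control group data". For the second, clinical ratio it says "ICER will also be calculated based on the cost per incremental caries arrested to assess cost-effectiveness".

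The section Calculation of Cost and Utility Weights makes QALYs the main effectiveness measure. On costs it says "Costs will be estimated as the product of unit costs and the quantity of resources" and "The treatment cost will include oral health examination cost, AgF application, and costs for any urgent conditions". Neither section writes the QALY ICER as a cost difference between arms over a QALY difference between arms.

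Under Intervention and in Table 1, both arms are examined at T1 and T2, and controls receive AgF at T2, the last scheduled assessment.

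**The concern.** An incremental ratio asks what one strategy costs, and gains, over another. The stated numerator is a total. The stated denominator, "differences in QALYs between baseline and postintervention for all participants", contrasts two times rather than two arms. A ratio built that way responds to things that have nothing to do with AgF: utility trends that both arms share, and examination costs that both arms incur.

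The time reference also does not fit the design. Controls are treated at T2 and not assessed afterwards, so a QALY change up to a point after treatment does not exist for them.

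Cost-effectiveness and cost-utility form one of the four listed objectives, and the threshold comparison rests on this ratio. If the sentence were followed as it stands, the value-for-money conclusion could be too favourable or too unfavourable.

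**Working it through.** The documents give no ICER, cost, utility or threshold, so there is no figure to reproduce. The check is of the definition. All costs, utilities and QALY changes below are assumptions, in arbitrary currency.

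**Notation.** C_I and C_C are mean costs per resident in the intervention and control arms. D_I and D_C are mean QALY changes. Arms are taken as equal in size (planned: 14 clusters × 25 completers = 350 per arm), so the number per arm cancels. Baseline utility is taken as equal in the two arms.

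- Between-arm ICER: (C_I − C_C)/(D_I − D_C)
- Literal ratio over all participants: (C_I + C_C)/(D_I + D_C)
- Literal ratio within each arm: C_I/D_I and C_C/D_C

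**Common costs and trends.** Add an examination cost e to both arms. The between-arm numerator is unchanged, while the literal numerator rises by 2e. Add a common QALY trend t to both arms. The between-arm denominator is unchanged, while the literal denominator moves by 2t. Cross-multiplying the first two formulas shows that they agree only when C_I·D_C = C_C·D_I, which in general does not hold.

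**Illustration of a shared time trend.** Assume costs of 150 and 60, T1 utility of 0.60 in both arms, T2 utility of 0.60 (AgF) and 0.58 (control), and linear change over 0.25 years. A utility change then converts to QALYs by the factor 0.25 × 0.5 = 0.125.

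- Between arms: (150 − 60)/(0.125 × 0.02) = 90/0.0025 = 36,000 per QALY.
- Literal, all participants: mean cost (150 + 60)/2 = 105; mean QALY change 0.125 × (0 − 0.02)/2 = −0.00125; ratio −84,000. Taken at face value, this is cost with a loss of QALYs.
- Add 0.03 to T2 utility in both arms (0.63 and 0.61). The between-arm ICER stays at 36,000. The literal ratio becomes 105/[0.125 × (0.03 + 0.01)/2] = 105/0.0025 = 42,000.

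**Direction of error.** The first five rows assume C_I = 150 and C_C = 100, so the literal ratio is 250/(D_I + D_C) and the between-arm ICER is 50/(D_I − D_C). The last row assumes C_C = 0.

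| D_I | D_C | Literal, all participants | Between-arm |
|---|---|---|---|
| 0.010 | 0.004 | 17,857 | 8,333 |
| 0.010 | −0.008 | 125,000 | 2,778 |
| 0.010 | 0.009 | 13,158 | 50,000 |
| 0.010 | 0.010 | 12,500 | undefined (no QALY effect) |
| 0.002 | −0.010 | −31,250 | 4,167 |
| 0.010 | 0 (C_C = 0) | 15,000 | 15,000 |

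The literal ratio can be too high, too low or of the wrong sign, and it stays finite when AgF has no effect on QALYs. The two agree in the last row, where control cost and control QALY change are both zero. Control costs will not be zero if the control examinations are costed.

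**Within-arm reading.** In the first row, the arm-specific ratios are 150/0.010 = 15,000 and 100/0.004 = 25,000. Neither is the between-arm 8,333. Applying the sentence arm by arm does not make it incremental.

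**The case against.** The strongest reply is that this is compressed wording. The Markov model takes data from both groups, and such a model is normally built to compare strategies. The ratio is called incremental, and so is the caries denominator. The Resident Survey section says the survey data, which include the EQ-5D-5L, will be tested against both baseline and a nonintervention control. The Quality of Life Outcomes section models the effect of group. The phrase about all participants may mean only that everyone contributes data to a later contrast.

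Much of this stands. A reader might infer that the plan pools the arms and discards the randomised comparison, so that the published value-for-money result would be wrong. The text does not go that far: it does not say that the arms are pooled, and the model could yield a proper ICER.

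It does not remove the point. Using both groups for transition probabilities does not define the ICER. The next sentence describes its construction, and it describes something else. On the charitable reading the section is inconsistent with itself and still needs correcting. Nor is this a detail left to a fuller plan, because the article states the ratio.

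Two further limits are fair. The figures above come from a simple 3-month calculation on assumed inputs, not from the planned model, so they show that the formulas differ and do not predict this trial's result. Prescribing a purely within-trial area-under-the-curve analysis would also go beyond the fault and would have to be squared with the Markov model.

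**Conclusion.** The point holds as a fault in a stated definition. Neither term of the QALY ICER, as written, is a between-arm difference, on either the pooled or the within-arm reading. The sentence also fits poorly with the Markov comparison and refers to an assessment after treatment that controls do not have.

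If it is followed literally, the ratio set against the threshold would depend on time trends and examination costs common to both arms, and could mislead in either direction. How far cannot be said from the documents; 36,000 against −84,000 or 42,000 is illustration under assumed inputs. That the final economic result will be wrong is not established, since the model may be run correctly despite the sentence. The clinical effectiveness analyses are unaffected.

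**What to change.** Restate the sentence as: ICER = (mean cost, intervention − mean cost, control)/(mean QALYs, intervention − mean QALYs, control), with both differences taken from the planned Markov comparison of the two strategies. Any QALY inputs estimated from trial data should be adjusted for baseline EQ-5D-5L utility and for facility clustering. State the same between-arm contrast for cost per additional caries lesion arrested, where the comparator is currently unnamed.

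The redefinition costs a sentence or two, plus modest analysis work for the adjusted inputs. No new data items are needed: Table 1 already schedules the EQ-5D-5L and cost information at T1 and T2. Data collection is projected to run to June 2026 and the economic report is planned for early 2027, so the wording can be settled before the economic analysis is reported.

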### Recruitment and Flow of the Study

Public and private aged care providers located in regional and rural Queensland and New South Wales, Australia, will be identified, approached, and provided with a Facility Participation Information and Consent Form prior to enrollment as study clusters. Once RACFs have consented, they will be randomly allocated in a 1:1 ratio to either the intervention or control arm using a computer-generated random sequence. Clusters assigned to the intervention arm will receive the AgF intervention at the first clinical visit, while those in the control arm will be offered the intervention after a 3-month delay. All individuals within a cluster will receive the same allocation condition. Study information materials, including leaflets and a short explanatory video, will be provided to participating RACFs for distribution within their facilities. Facility staff will identify and approach potentially eligible residents and coordinate scheduling with the study coordinator.

Upon arrival at the facility, the research team will meet with residents (and, where applicable, their Enduring Power of Attorney) to provide a detailed explanation of the study, confirm eligibility, and obtain written informed consent. Where there are any communication difficulties, RACF staff will be engaged to assist with facilitating communication. Once written informed consent has been obtained, the research team will administer a questionnaire, conduct an oral examination, and administer the AgF intervention in accordance with the study protocol.

For individuals requiring urgent dental care or identified as high risk of rapid oral health deterioration, regardless of their allocation, RACF staff will be advised by the research team clinicians, and referral will be made to their care facility to initiate appropriate action to access dental treatment. This does not exclude individuals from participating in the study.

At 3 months, the study coordinator will coordinate follow-up assessments with participating facilities. Ongoing consent will be confirmed with participants (and, where applicable, their Enduring Power of Attorney) prior to follow-up procedures.

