### Intervention

AgF will be the intervention treatment used in this study. The first of the 2 bottles of the SDI Riva Star Aqua system (manufactured by Southern Dental Industries Ltd.), which contains 38% aqueous AgF, will be applied. This corresponds to step 1 of the manufacturer’s 2-step procedure. The decision to use only the first bottle is intended to simplify the application process and reduce treatment time. Using the first bottle of AgF ensures the evidence is relevant for generic AgF products, which is important for wider implementation of the findings.

At time 1 (the initial appointment, T1), all consented participants will undergo an oral examination to assess oral conditions and identify teeth requiring AgF treatment.

In an oral environment with a high risk of caries (eg, salivary gland hypofunction, acidic mouth pH), root surfaces and exposed dentin are at increased risk of dental caries developing. For participants assessed as being at high-risk of oral health issues developing, referral and discussion with the nurse coordinator at the facility will be undertaken as appropriate.

Participants in the intervention group will receive AgF during this first appointment. In contrast, participants in the control group will receive the same treatment at the 3-month follow-up appointment. AgF will be applied by the research team’s trained oral health professionals.

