### Resident Participant Timeline

Table 1 presents the participant timeline for the cluster randomized controlled trial of AgF, including the intervention and control groups. Residents who elect to participate will be invited to provide informed consent. At baseline (T1), all participants will receive an oral health assessment and complete a demographic, quality of life, and oral health survey (Table 1). Those allocated to treatment will also receive an AgF application. At the 3-month follow-up, all participants will receive the oral health assessment and survey again; control group participants will receive the AgF application.

**Table 1. T1:** Resident participant timeline for the cluster randomized controlled trial of silver fluoride, showing intervention group and control group.

Procedures	Study period		
	Enrollment	T1	T2
Enrollment			
Consent (self, legal guardian, or NCAT^a^, QCAT^b^)	✓		
Exclusion criteria	✓		
Allocation (cluster)	✓		
Survey			
Demographics and oral health history		✓	✓
Quality of life (EQ-5D-5L) [36]		✓	✓
Geriatric Oral Health Assessment Index (GOHAI) [37]		✓	✓
Intervention			
Intervention clusters: AgF applications for clinically indicated teeth at T1		✓	
Control clusters: AgF applications for clinically indicated teeth at T2			✓
Summary of data collection			
Oral clinical assessment (dental caries experience; dentin exposure; tooth sensitivity; oral hygiene status; oral mucosal conditions; salivary status)		✓	✓
Oral health–related quality of life		✓	✓
Quality of life		✓	✓
Demographics	✓		
General health, medications, and diet		✓	✓
Health economic information: cost and referral uptake		✓	✓
Health economic information: participant experience		✓	✓

a NCAT: NSW Civil and Administrative Tribunal.

b QCAT: The Queensland Civil and Administrative Tribunal.

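### The economic conclusion concerns providing dental care to residents, but the randomised contrast covers only AgF at T1 versus AgF delayed to three months, given an examination and referral that both arms receive

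*Protocol article*

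**What the plan says.** The protocol article's Health Economic Analyses section opens with a narrow question: "The cost-utility and cost-effectiveness of the intervention will be evaluated from a health service perspective". Later in the same paragraph the conclusion is wider: "The value for money of the provision of dental care to RACF residents will be assessed by comparing the estimated ICER" with a threshold for a QALY. The ICER is worded as a ratio of total costs to the change in QALYs from before to after the intervention across all participants. The transition probabilities of the Markov model come from both arms.

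On cost, Calculation of Cost and Utility Weights states: "The treatment cost will include oral health examination cost, AgF application, and costs for any urgent conditions".

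On what each arm receives:
- Intervention: at T1, "all consented participants will undergo an oral examination to assess oral conditions and identify teeth requiring AgF treatment".
- Resident Participant Timeline: "At baseline (T1), all participants will receive an oral health assessment and complete a demographic, quality of life, and oral health survey". Table 1 shows the same.
- Recruitment and Flow of the Study, for residents with urgent need or at high risk of rapid deterioration: "regardless of their allocation, RACF staff will be advised by the research team clinicians, and referral will be made to their care facility".
- Intervention, on the delayed arm: "participants in the control group will receive the same treatment at the 3-month follow-up appointment".

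**The concern.** An ICER answers the question set by its comparator. To judge whether providing dental care to residents is worth its cost, the comparator is residents who receive no visiting service. The section on the gap in current knowledge describes conventional care as hard to reach for this population, so that comparator is realistic. The trial does not contain it, because every control resident is examined by a visiting professional and urgent problems are passed on for action.

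The risk is that a funder reads the threshold comparison as a verdict on starting a visiting service, when the randomised data address only whether to apply AgF once the visit has taken place. The Discussion expects the trial to inform scalability and policy, so the difference matters to the likely reader. The documents do not say that the ICER alone will be used for that purpose.

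**Working it through.** The article states no ICER, arm cost, examination fee or threshold value, so there is no figure to reproduce. The check sets the arms side by side and then writes out the cost and QALY identities.

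**1. What each arm receives up to the T2 assessment**

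| Component | Intervention arm | Control arm | Source |
|---|---|---|---|
| Examination at T1 | yes | yes | Intervention; Resident Participant Timeline; Table 1 |
| Advice and referral if urgent | yes | yes | Recruitment and Flow of the Study |
| AgF | at T1 | not until the 3-month visit | Intervention; Table 1 |

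**2. Between-arm reading.** Per resident, let E be the examination cost, A the cost of AgF application and U the cost of urgent care. Let b be the QALY gain from examination and referral, and q the further gain from AgF.

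- Intervention cost = E + A + U_int
- Control cost = E + U_ctl
- Cost difference = A + (U_int − U_ctl)
- QALY difference = (b + q) − b = q

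E and b cancel whatever their values. Urgent care is available to both arms, but its cost cancels only if its use is equal. A real difference in use belongs in the increment.

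**3. What a provision conclusion needs.** Against no visit, the cost increment is E + A + U_int minus usual-care cost, and the QALY increment is b + q. The trial observes neither usual-care cost without a visit nor b. The control arm's before-after change does not give b, because it mixes any benefit of the visit with the natural course over three months.

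**4. Literal reading.** Total cost over the pooled before-after QALY change keeps E in the numerator but compares with nothing. As an illustration only, assume E = 100, A = 50, equal arms and U set aside. Mean cost up to T2 is then 100 + 50/2 = 125.

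| QALY change, intervention / control | Pooled ratio | Pooled, delayed AgF also costed | Between-arm ratio |
|---|---|---|---|
| 0.010 / 0.004 | 125 / 0.007 = 17,857 | 150 / 0.007 = 21,429 | 50 / 0.006 = 8,333 |
| 0.010 / 0.008 | 125 / 0.009 = 13,889 | 150 / 0.009 = 16,667 | 50 / 0.002 = 25,000 |

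The ordering of the two readings reverses with the control arm's change, so neither can stand in for the other.

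**5. Direction of error against the provision question.** Take U equal and usual-care cost zero for simplicity. The provision ratio is (E + A)/(q + b) and the between-arm ratio is A/q. The first is larger only if E/b > A/q. With E = 100, A = 50 and q = 0.006, A/q = 8,333, and the two ratios are equal at b = 100/8,333 = 0.012 (check: 150/0.018 = 8,333). For smaller b the between-arm ratio is too favourable as an answer about provision; for larger b it is too unfavourable. Since b is not observed, the direction is open.

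**The case against.** The strongest reply is that this is one loose phrase. Objective 3 and the opening of Health Economic Analyses both name the intervention as the thing evaluated. The article also condenses an economic evaluation that belongs to a wider programme and will be reported separately, so model strategies and comparators may be set out elsewhere. That stands as a limit on what can be asked: the absence of a full model specification is no fault here. It does not remove the point, because the wider conclusion is stated, it is the one compared with the threshold, and the stated design cannot support it.

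A reader might go further and infer that the ICER omits the examination cost and therefore flatters the service by a calculable multiple. The documents do not support that:
- The examination is listed as a cost, and the ratio as worded uses total costs for all participants. The cost drops out only under a between-arm increment, which the text suggests (the ratio is called incremental, and both arms feed the model) but does not state.
- In a Markov model, costs are attached to strategies. Nothing says whether the comparator strategy will be charged for the examination.
- Any multiple rests on assumed fees. The ratio (E + A)/A runs from 1.5 (E = 50, A = 100) to 21 (E = 200, A = 10), and none of these values is in the article. Counting AgF material alone would push it higher, but trained professionals apply the agent and labour is to be costed.
- A cost multiple is not an ICER multiple, because moving to a no-visit comparator changes the QALY difference as well.

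**Conclusion.** The point holds as a mismatch between the stated economic conclusion and the randomised contrast. The trial can identify the value of AgF at T1 versus none until the 3-month visit, given examination and referral. It cannot identify the value of providing dental care, whether the ICER is read as a between-arm increment or as the pooled before-after ratio.

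This rests on the arms differing by design only in AgF up to the T2 assessment, which the article states consistently. The size and direction of the error in the ICER cannot be derived from the article; the figures in the working are illustrations on assumed inputs. The consequence is limited to what the economic evaluation may claim. The clinical comparisons are unaffected.

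**What to change.** In Health Economic Analyses, define the ICER as the between-arm difference in cost divided by the between-arm difference in QALYs, both up to the T2 assessment. Replace the reference to providing dental care with adding AgF to an on-site examination and referral visit.

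If a conclusion about provision is still wanted, present it only as a clearly labelled model scenario against no visit, with external assumptions stated for both the cost and the benefit of examination and referral. Charging the examination cost to the AgF strategy while leaving its benefit out would be one-sided.

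The core change takes a sentence or two and no new data. Its price is a narrower economic conclusion. The optional scenario costs one extra model strategy and sourced inputs.

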### Sample Size Calculation

The primary outcome of AgF effects on dentin hypersensitivity was used for the sample size calculation. Based on estimates presented by Chan et al [23] and Castillo et al [32] assessing AgF effects on dentin hypersensitivity using a visual analog score, a mean difference of 2.9 units with a SD of 2.6 indicates that a total of 8 clusters (4 per arm) is required to achieve statistical power greater than .80 (*β*>.80), assuming a significance level of .05 (*α*=.05) and 25 participants per cluster. To account for potential attrition, we plan to increase the cluster size by at least 50%, resulting in 40 participants per cluster at baseline. This would yield 160 participants in each group, for a total of 320 participants.

Given the absence of known adverse health effects from AgF and the likelihood that participants will benefit from access to an otherwise unavailable health intervention, we propose overenrolling sites. Specifically, the aim is to recruit 28 clusters (14 per arm), with up to 40 participants per site. This will improve the precision of our estimates of efficacy. This oversampling is planned to account for potential within-facility clustering in residential aged care settings.

Assuming 25 participants per site complete both baseline and follow-up assessments and using a conservative intracluster correlation coefficient (ICC) of 0.15, this sample size will allow detection of an effect size of approximately 0.48 (Cohen *d*) [33]. For categorical outcomes, this sample would be powered at 0.80 to detect a 23% difference between groups, assuming a 50% control group proportion.

Using more precise parameters for this study design, 28 clusters with 25 individuals providing complete data and an individual autocorrelation of 0.5, the minimum detectable effect size decreases to 0.20 (mean difference divided by SD). For categorical outcomes, the same design would be powered at 0.80 to detect a 10% absolute difference, again assuming a control proportion of 0.5.

All sample size and power calculations were informed by Hemming et al [34] and conducted using the Shiny CRT Calculator: Power and Sample Size for Cluster Randomized Trials.

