### Limitations and Considerations

Several limitations should be acknowledged. First, a 3-month follow-up period may limit the assessment of long-term caries progression or sustained quality-of-life effects. However, short-term outcomes are clinically relevant in frail populations where rapid deterioration may occur [44]. Second, clustering at the facility level may introduce variability related to care models or specific types of each facility; this will be addressed analytically using mixed-effects regression models that account for facility-level random effects. Third, participation may be influenced by consent processes, particularly among residents with cognitive impairment, which may affect generalizability. Finally, as a pragmatic trial, some variability in RACFs in terms of staff ratios or facility priorities is expected. However, this reflects real-world conditions and strengthens external validity.

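### Judging value for money by the ICER against a threshold misreads any negative QALY difference and is undefined at zero; net monetary benefit should be the stated criterion

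*Protocol article*

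**What the plan says.** The relevant text is in two sections of the Protocol article.

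- **Calculation of Cost and Utility Weights.** QALYs are the main measure of effectiveness, and "the utility weights to generate QALYs will be informed by the EQ-5D-5L scores", valued with Australian weights. The participant timeline (Table 1) has the EQ-5D-5L collected at T1 and T2 only.
- **Health Economic Analyses, model.** "A Markov model will be developed using TreeAge Pro software (TreeAge Software Inc.), and the cycle length will be 1 month". Transition probabilities come from the two trial arms. No time horizon is given.
- **Health Economic Analyses, ICER.** It is built from "The ratio of estimated total costs and differences in QALYs between baseline and postintervention for all participants".
- **Health Economic Analyses, criterion.** Value for money "will be assessed by comparing the estimated ICER with the willingness-to-pay threshold for a QALY". The threshold is not given a value. Nothing is said about a zero or negative QALY difference, dominance, net benefit or an acceptability curve.
- **Health Economic Analyses, uncertainty.** "A probabilistic sensitivity analysis will be conducted to determine the robustness of the cost-utility and cost-effectiveness findings". How the draws will be turned into a statement about value for money is not described.

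On precision, Sample Size Calculation says "the aim is to recruit 28 clusters (14 per arm), with up to 40 participants per site" and assumes 25 completers per site. Limitations and Considerations accepts that "a 3-month follow-up period may limit the assessment of long-term caries progression or sustained quality-of-life effects".

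**The concern.** An ICER is a ratio, and its sign alone does not show where a result lies on the cost-effectiveness plane. A negative ICER arises both when AgF saves money and gains QALYs (clearly good) and when it costs more and loses QALYs (clearly bad). A positive ICER below the threshold arises both when AgF buys QALYs cheaply and when it gives up QALYs for too small a saving. A rule stated only as ICER against threshold does not separate these cases.

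Cost-utility is a stated objective and the results are meant to inform policy. If the QALY difference comes out negative, the stated comparison followed to the letter can support AgF when the data point the other way, or reject it when they favour it. The same applies to each draw of the sensitivity analysis if draws are counted by whether their ICER is below the threshold.

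**Working it through.** **1. Where the rule holds and where it fails.** Let ΔC and ΔQ be the between-arm differences in cost and QALYs, and λ the threshold. AgF is good value when λΔQ − ΔC > 0.

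- If ΔQ > 0, dividing by ΔQ gives ΔC/ΔQ < λ, and the stated comparison gives the right decision. (If AgF is also cheaper, the ratio is negative and no longer reads as a price per QALY.)
- If ΔQ < 0, dividing reverses the sign, and the correct condition is ΔC/ΔQ > λ. The stated comparison then gives the opposite decision.
- If ΔQ = 0, the ratio does not exist, while net benefit is simply −ΔC.

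**2. Numerical illustration.** λ = 50,000 per QALY is an assumption, because the article names no threshold. The cost and QALY differences are also chosen for illustration.

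| ΔC | ΔQ | ICER | ICER below λ? | Net benefit = λΔQ − ΔC | Correct decision |
|---|---|---|---|---|---|
| +100 | +0.005 | 20,000 | yes | 250 − 100 = +150 | accept |
| +100 | +0.001 | 100,000 | no | 50 − 100 = −50 | reject |
| −100 | +0.005 | −20,000 | yes | 250 + 100 = +350 | accept |
| +100 | −0.005 | −20,000 | yes | −250 − 100 = −350 | reject |
| −100 | −0.005 | 20,000 | yes | −250 + 100 = −150 | reject |
| −100 | −0.001 | 100,000 | no | −50 + 100 = +50 | accept |

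The first three rows agree with net benefit. The last three, all with a negative QALY difference, do not.

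**3. The plan's own precision, reproduced.** Inputs from Sample Size Calculation: 14 clusters per arm, 25 completers each (14 × 25 = 350 per arm), ICC 0.15, alpha 0.05 (taken as two-sided), power 0.80.

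- Design effect: 1 + 24 × 0.15 = 4.6.
- Standard error of a standardised difference: √(2 × 4.6/350) = 0.162.
- Detectable effect: 2.802 × 0.162 = 0.454 with normal quantiles, or 0.472 with t on 26 degrees of freedom. The article states about 0.48.
- With baseline measurement, individual autocorrelation 0.5 and cluster autocorrelation assumed to be 1: r = (25 × 0.15 + 0.85 × 0.5)/4.6 = 0.908. Multiplying the standard error by √(1 − r²) gives a detectable effect of 0.191 (normal) or 0.198 (t). The article states 0.20.
- Standard error implied by the stated 0.20: 0.20/2.802 = 0.071.

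Both stated figures reproduce closely, so 0.162 and 0.071 bracket the precision that the plan claims.

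**4. Chance that the estimated difference is at or below zero.** For a true standardised EQ-5D effect d, this is Φ(−d/SE).

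| True d | SE 0.162 | SE 0.071 |
|---|---|---|
| 0 | 50% | 50% |
| 0.05 | 38% | 24% |
| 0.10 | 27% | 8% |
| 0.20 | 11% | 0.3% |
| 0.48 | 0.2% | about 0% |

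This treats the sign of the utility difference as the sign of the QALY difference and applies the article's general ICC to EQ-5D. It is an illustration and does not predict the Markov model's output.

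**The case against.** The strongest reply is that comparing an ICER with a threshold is the customary short description. The article nowhere says that every ICER numerically below the threshold counts as good value, whatever its sign. A competent health economist would recognise dominance, and a condensed article may leave that to a fuller economic plan. This has force and limits the weight of the point. It does not remove it, because the article does fix a criterion, and that criterion gives no guidance over part of the range the data can produce.

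A reader might also infer that a zero or negative QALY difference is likely with 3 months of follow-up and 28 facilities. The documents do not support that. The chance depends on a true effect that is not stated, is below 50% for any positive effect, and is small at d = 0.20. The QALYs come from a Markov model with an unstated horizon, so the 3-month follow-up alone does not set the size or sign of the modelled difference.

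For the same reason I put no weight on simulated rates of false-favourable verdicts. Under an assumed utility SD of 0.25, linear change over 3 months, a threshold of 50,000 and an extra cost of 50 to 150 per resident, the literal rule favours AgF in 61% to 92% of no-effect trials, against 11% to 42% under net benefit. Those inputs are not in the article, and the calculation is a within-trial one, not the planned model.

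It would also be too strong to say that the sensitivity analysis is certain to inherit the fault. The article does not say how draws will be classified, so the analysis could repeat the error or avoid it. Finally, quality of life is a coprimary outcome analysed by group, so a clearly adverse effect should be visible beside any ICER. That is a partial safeguard, but it does not correct the value-for-money statement itself.

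**Conclusion.** The point holds as a defect in the stated criterion. With a negative QALY difference, comparing the ICER with the threshold gives the opposite of the correct decision, and at zero there is no ICER to compare. This is algebra and rests on no assumed input.

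How often it would matter is uncertain. It is a material risk if the EQ-5D effect is small: 50% at no effect and roughly 8% to 27% at d = 0.10. It is a minor one if the effect is moderate: 0.3% to 11% at d = 0.20. These figures carry the assumptions given with the calculation.

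The wording of the ICER adds to the exposure. Taken literally, its denominator is a before-after change pooled over all participants. In a frail population that includes residents with terminal illness (Ethical Considerations), such a change could be negative through ordinary decline, whatever AgF does. The clinical effectiveness analyses are unaffected.

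**What to change.** Replace the criterion in Health Economic Analyses along these lines:

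- Value for money will be judged by the between-arm incremental net monetary benefit, which is the threshold times the between-arm QALY difference minus the between-arm cost difference, at a named threshold. It will be computed from the planned Markov model.
- It will be reported with its uncertainty interval and with the share of probabilistic sensitivity analysis draws in which net benefit exceeds zero.
- The ICER will be reported only when AgF is both costlier and more effective. Otherwise the report will state dominance or name the quadrant.

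Defining both differences between arms also removes the pooled before-after denominator. A within-trial estimate of net benefit from a mixed model with facility random effects may be added as a supplementary analysis. It should not replace the planned model.

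The cost is a small amount of extra analysis and reporting. No new data are needed, and a threshold has to be named under the present criterion anyway. Results places the economic report in early 2027, so the change can be made before that analysis.
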